### Data Analysis

Participant characteristics will be compared between the group receiving the individual music intervention and the group receiving CAU. Further analyses will be adjusted for any potential significant differences. The primary analyses will be undertaken on an intention-to-treat basis, and 2-sided tests will be applied at a 5% α level. In addition, per-protocol analyses will be conducted based on the sample of participants who adequately adhered to the intervention protocol by completing at least 12 of the 16 music sessions (ie, 75%), which is similar to 67% and 80% of 2 other intervention studies among adults with mild to moderate ID [67,68]. In addition, by setting the threshold at 12 sessions, we know for sure that all intervention participants followed at least 1 or 2 sessions with a focus on emotions and EF.

To minimize the number of analyses on outcome domains, the 4 different EF measures will be converted into *z* scores and, according to factor analysis, summed up into an EF domain if possible. Subsequently, to test differences in changes from baseline to follow-up between the 2 conditions, a linear mixed model analysis for each treatment variable will be used. Within each analysis, only time and the interaction between the treatment variable and time will be used [69], making it possible to adjust for the dependence of the repeated observations within the subjects. The effect of the intervention on the 2 follow-up measurements will be assessed. This analysis allows for participants with only a baseline measurement but with missing data at follow-up to be included. The normality of the residuals from the linear mixed model analysis will be visually inspected.

Secondary analyses will be performed as well. The effect of extra music interventions will be tested applying a Mann-Whitney *U* test for the between-group comparisons. The self-reported feelings before and after each music session will be compared using a Wilcoxon signed rank test.

Descriptive statistics will be used to summarize the quantitative data of the log reports, evaluation questionnaires, and the follow-up evaluation.

Qualitative data of log reports, evaluation questionnaires, follow-up evaluation, recruitment log, trial log, and semistructured interviews will be analyzed using thematic context analysis on multiple aspects of the intervention and the overall study process, including recruitment, retention, acceptability or satisfaction, maintenance, dose, fidelity, reach, adaptation, and context.

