### Procedure

Participants will be recruited from residential facilities for people with ID of the Philadelphia Care Foundation throughout the Netherlands. Because participating in this study requires time and effort of their staff, care managers of facilities serving adult residents with mild to moderate ID are contacted about their willingness to participate in the study. Managers with interest will receive an information letter explaining the research aims and responsibilities of all parties involved. Next, the special psychologist of the facility will check which residents are eligible for inclusion, who then will receive an information letter and an informed consent form in a Dutch easy-to-read format [40]. Caregivers will be asked to read the letter together with potential participants and help them to fully understand the text, if needed. Legal representatives of the eligible residents will also receive an information letter and an informed consent form, whereas nonlegal representatives of the eligible residents will only receive an information letter. Residents will only become participants in the study if (both) informed consent forms are signed. Subsequently, the special psychologist of the facility will be asked for the participant characteristics, which are age, gender, level of ID, syndrome (when applicable), and comorbid psychiatric diagnoses.

After all assessments are completed, participants will receive a compliment postcard from the Philadelphia Care Foundation and a gift card of €15 (US $17.82 when enrollment commenced).

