### Sample Size Calculation

The sample size is calculated using G*Power software (version 3.1.9.7) [66]. The sample size calculation is based on a small effect size of 0.2, a statistical power of 0.95, and a type I error probability of α=.05, which results in an unadjusted sample size of 67 participants. Because cluster randomization negatively affects the power, the sample size needs to be adjusted. With the average cluster size of 2 participants per residential facility and allowing an intraclass correlation of 0.2, the adjusted sample size is 80. To allow for a dropout rate of 20% over the course of the study, we will aim at recruiting a total of at least 96 participants.

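### Covariates are to be chosen by significance tests on baseline characteristics, so the primary model is not fixed in advance and moderate imbalances in prognostic variables go unadjusted

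*Protocol article*

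**What the plan says.** The first paragraph of Data Analysis in the protocol article sets out two steps. First, "Participant characteristics will be compared between the group receiving the individual music intervention and the group receiving CAU". Then, "Further analyses will be adjusted for any potential significant differences". The same paragraph says that "2-sided tests will be applied at a 5% α level". No separate level is given for the baseline comparison, so 5% is the natural reading.

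The Procedure section lists what is collected: "participant characteristics, which are age, gender, level of ID, syndrome (when applicable), and comorbid psychiatric diagnoses". None of these is named in advance as a covariate.

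The second paragraph of Data Analysis describes the linear mixed model: "Within each analysis, only time and the interaction between the treatment variable and time will be used". The article does not say whether covariates picked up by the baseline comparison are added to this model, or whether an adjusted analysis would be primary or supportive.

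**The concern.** The article states a covariate-selection rule, so this is not a detail left open for an analysis plan. The rule has three weaknesses.

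- Under randomisation, any baseline difference is due to chance. A significance test of it answers no useful question, and its result depends on sample size and not on whether the variable predicts the outcome. A predictive variable with a moderate imbalance is left out; an irrelevant one with a large chance imbalance is put in.
- The covariate set is unknown until the arms have been compared. The trial is unblinded and has many outcomes, so the primary model should be settled before that.
- Read literally, the sentence limiting the model to time and treatment-by-time leaves no room for the covariates that the earlier sentence would add. Two analysts could each follow the text and report different primary estimates.

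**Working it through.** **Inputs.** 44 intervention and 53 control participants (Abstract and Results). Five characteristics (Procedure). Two-sided 5% level (Data Analysis). The correlations below are assumptions, since the article gives none.

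**1. Size of imbalance that triggers adjustment, continuous characteristic.**
- Standard error of the difference in SD units: √(1/44 + 1/53) = √0.0416 = 0.204.
- Critical t on 95 degrees of freedom: 1.985. Threshold: 1.985 × 0.204 = 0.405, about 0.40 SD.
- An observed difference of 0.3 SD gives t = 0.3/0.204 = 1.47, below 1.985, so it is not flagged.

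**2. The same for a binary characteristic** (z test with pooled proportion).
- With 26/53 (49.1%) in control, the first significant count above it in the intervention arm is 31/44 (70.5%), a gap of 21.4 percentage points.
- With 16/53 (30.2%), it is 22/44 (50.0%), a gap of 19.8 points.
- Smaller gaps in that direction would be left unadjusted.

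**3. Chance triggers.** With five independent tests at 5%: 1 − 0.95⁵ = 1 − 0.774 = 0.226, about 23%. Positively related characteristics would lower this.

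**4. Effect of an unadjusted imbalance.** The shift in the estimated treatment effect is roughly the imbalance times the correlation between characteristic and outcome, once baseline outcome is accounted for.
- Imbalance 0.3 SD, correlation 0.2: 0.3 × 0.2 = 0.06 SD.
- Imbalance 0.3 SD, correlation 0.5: 0.3 × 0.5 = 0.15 SD.

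The SD is that of the outcome after allowing for baseline. The shift is conditional on that imbalance having occurred; over all randomisations it averages to zero.

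**5. Precision forgone.** Adjusting for such a characteristic multiplies the residual variance by about 1 − r². That is 0.96 at 0.2 and 0.75 at 0.5, so the standard error is multiplied by about 0.98 and 0.87.

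**6. Type I error.** Check by 40,000 simulated trials with 44 and 53 independent participants, no treatment effect and one normally distributed characteristic:

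| Analysis | r = 0.5 | r = 0.7 |
|---|---|---|
| Characteristic always in the model | 5.1% | 4.9% |
| Test first, adjust only if significant | 4.4% | 3.5% |
| Unadjusted test, when baseline \|t\| lies between 1 and the critical value | 7.3% | 8.6% |

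Overall, the rule is slightly conservative. Error exceeds 5% only within the trials that had a moderate, unflagged imbalance. The simulation has no clustering and no repeated measures.

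**The case against.** The strongest reply is that the practical harm is limited. A model with time and treatment-by-time but no treatment main effect already deals with baseline differences in the outcome itself. What remains concerns the other characteristics, whose association with change may be weak. This stands, and it is why the shift is given as a range resting on an assumption.

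Several stronger readings are tempting, but the article does not support them.

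- *The two rules flatly contradict each other.* They stand in successive paragraphs. The statement that "only time and the interaction between the treatment variable and time will be used" may mean no more than that the treatment main effect is omitted, with covariates added on top. The text needs reconciling; it is not certainly inconsistent.
- *False positives are inflated.* Overall they are not, as step 6 shows.
- *A shift of 0.15 nearly equals the target effect.* The sample size is "based on a small effect size of 0.2, a statistical power of 0.95, and a type I error probability of α=.05", with the type of effect size unnamed. As a standardised difference in a simple two-group comparison, 0.2 at 95% power needs 650 per arm. The stated 67 is matched by f² = 0.2 with one predictor (67), and closely by f = 0.2 with three time points and an assumed correlation of 0.5 (66). The two figures may be on different scales and should not be compared.
- *The baseline tests ignore clustering, or randomisation was unstratified.* The article does not name the baseline test. It describes randomisation by facility without saying whether it was stratified. Neither can be asserted from silence.
- *Age, gender and level of ID are known to be prognostic.* The Background links mental age to executive functioning, but the article does not show that these variables predict each outcome.

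**Conclusion.** The point holds as a weakness in a stated rule, and it should be corrected before analysis. Selection by baseline significance leaves every observed imbalance below about 0.40 SD unadjusted (about 20 to 21 percentage points in the binary examples), whatever its prognostic weight. It brings in at least one covariate by chance in about 23% of trials if the five characteristics are independent. For a 0.3 SD imbalance and assumed correlations of 0.2 to 0.5, the conditional shift is 0.06 to 0.15 SD.

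The consequences are lost precision, conditional bias and a primary model that depends on the data. A higher overall type I error is not among them. How the adjustment rule fits the sentence restricting the model terms is unclear and must be stated.

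**What to change.** - Delete the significance-triggered adjustment.
- Before analysis, name a small covariate set chosen on expected prognostic value from the characteristics already collected, for example age, gender and level of ID. Give a one-line reason for each. Use the same set for every outcome, whatever the baseline p-values.
- Amend the model sentence to say that these covariates are added to time and treatment-by-time, and whether they enter as main effects only or also by time.
- Describe baseline characteristics by arm without tests.
- Report the model without covariates as a sensitivity analysis.

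The cost is a few sentences and a few degrees of freedom: three if age is linear and gender and level of ID are each binary. No new data are needed. The article says that analysis waits for acceptance of the protocol, so on its own account the change could still be made before results were seen.

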## Methods

### Study Design

This study is an RCT with a pretest (T1), posttest (T2, 9 weeks after T1, unless the last intervention session was not yet completed; posttest was postponed by 1 or 2 weeks until the week after the final session), and follow-up assessment (T3, 8 weeks after T2), including 2 groups of individual participants (see Figure 1). Participants belonging to the music condition will receive 16 individual music sessions within 8 to 10 weeks, and participants belonging to the control condition will receive (individual) CAU. Randomization will be performed at a facility level for 3 reasons: first, to prevent possible interference between participants belonging to both groups in a facility; second, it is deemed unethical and difficult to explain to people with ID who are assessed to the control condition that they have to wait for the music sessions, whereas fellow residents already receive them; finally, it can also promote recruitment [17]. For randomization, a computerized random number generator will be used. There is no maximum number of participants per facility. Blinding is not possible because it is clear to the caregivers, participants, and research assistants which type of intervention a participant receives. The independent research assistants are also not blinded because the participants of the music intervention have to fill in an extra questionnaire at the second and third assessment.

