In the manual, intervention procedures are specified, such as the setting, general goals, contents of the music sessions, basic principles of the intervention, and exemplifications. An outline of the music session can be seen in Table 1. Every session will be centered around a different aspect (introduction, emotions, different EF, and end performance), and in the training manual, example exercises are described focusing on every aspect. These examples are provided by advisory groups of professional music coaches and stem from different other manuals [41-43]. Each session will start with a welcome song, after which a listening exercise will take place. Then, a warm-up of the voice and body is scheduled, and subsequently, participants actively engage in music activities by singing or playing an instrument, after which a cool-down and a farewell song are performed. The manual provides a fixed frame for the intervention, but it leaves enough flexibility to tailor the intervention to the characteristics and needs of every participant. Participants will receive a diploma at the final session.

To study for exploratory purposes the impact of the music sessions’ frequency, some participants will receive extra music sessions, resulting in 24 to 27 sessions within the same time period, aiming at approximately 3 sessions a week.

**Table 1 table1:** Outline music session.

Music intervention	Time (minutes)	Attendees
Preliminary meeting	30	Music worker, participant, and caregiver
Music session 1: Welcoming or introduction 2-6: Emotions 7+10: EF^a^ (Inhibition) 8+11: EF (Cognitive flexibility) 9+12: EF (Working memory) 13-15: Working toward the end performance or song 16: End performance or song	60	Music worker and participant
Final meeting	30	Music worker, participant, and caregiver

^a^EF: executive functioning.

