#### CAU Group

Participants receiving CAU will function as a control group. CAU includes regular care such as assistance with acts of daily living and day care activities. CAU can include musical activities that participants already performed before the start of this study, as music is a central theme of the Philadelphia Care Foundation. However, new individual musical activities will be postponed for these participants until after the follow-up measurement. Participants receiving CAU will be offered a budget at the end of the study, which they can spend on musical activities or musical instruments to their own wishes, with the help of a musical specialist who works at the Philadelphia Care Foundation.

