#### Evaluation per Music Session

The music worker will ask the participant before and after each music session how he or she feels at that moment: happy, sad, scared, angry, or tired. Sheets representing 5 emoticons with associated feelings are shown to help the participant. If possible, the participant also indicates whether this feeling is little, normal, or intense. When it is too difficult for a participant to choose a specific emotion, the participant is asked whether he or she feels pleasant or nonpleasant.

Music workers will also complete a log report after each music session. The log report contains questions about that specific session: whether the session was performed according to the manual and how much time was spent on active music making.

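### The supportive per-protocol analysis excludes low attenders from the music arm only, so it is not a randomised comparison; a complier-average effect should be added and the per-protocol result labelled descriptive

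*Protocol article*

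**What the plan says.** The Data Analysis section of the protocol article sets the hierarchy: "The primary analyses will be undertaken on an intention-to-treat basis, and 2-sided tests will be applied at a 5% α level". Per-protocol analyses are added, "based on the sample of participants who adequately adhered to the intervention protocol by completing at least 12 of the 16 music sessions", a share given as 75%. Two reasons are offered for the cut-off. It resembles thresholds in two other intervention studies, and it secures exposure to the content: "we know for sure that all intervention participants followed at least 1 or 2 sessions with a focus on emotions and EF".

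No adherence rule is given for controls, and none of this kind could apply to them. Under Study Design, "participants belonging to the control condition will receive (individual) CAU", and under CAU Group, "new individual musical activities will be postponed for these participants until after the follow-up measurement".

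Two further statements bear on the point. Under Music Intervention Group, "some participants will receive extra music sessions, resulting in 24 to 27 sessions within the same time period". Under Evaluation per Music Session, "Music workers will also complete a log report after each music session", so attendance can be counted for each participant.

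**The concern.** The per-protocol set is defined by behaviour after randomisation that only one arm can show. A participant who would stop attending is removed if allocated to music and kept if allocated to care as usual. The article does not say in words that all controls stay in, but no other reading is workable.

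The planned mixed model does not repair this. It contains time and treatment-by-time only, with no treatment main effect, and so relies on randomisation for equal baselines; one-sided exclusion breaks that. Baseline adjustment removes selection that runs through the baseline score, but not selection on what happens afterwards. The planned adjustment for significant differences in participant characteristics has the same limit.

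At stake is the only planned analysis of the effect of adequately receiving the intervention. It will be read beside the intention-to-treat result, and the section gives no caution on how to interpret it.

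**Working it through.** **Figures in the plan.** 12/16 = 75%, as stated. Table 1 has five emotion sessions (2-6) and six EF sessions (7-12). Missing any four of the 16 leaves at least 5 - 4 = 1 emotion session and 6 - 4 = 2 EF sessions, so the content claim holds for the 16-session schedule. Against the longer schedules, 12/24 = 50% and 12/27 = 44%. The article gives no figure for the bias or power of the per-protocol analysis.

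**Inputs from the article.** 44 music and 53 control participants (Abstract, Results); facility randomisation (Study Design); average cluster size 2 and intraclass correlation 0.2 (Sample Size Calculation); two-sided 5% tests (Data Analysis).

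**Assumed inputs, not in the article.** Pre-post correlation 0.6; share q reaching 12 sessions 70-90%; correlation r of 0.3-0.5 between attendance propensity and the part of the later score not explained by baseline; no true effect.

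**Bias.** The residual SD after baseline adjustment is √(1 - 0.6²) = 0.8. With a normal attendance propensity cut so that a share q lies above the threshold z, the mean propensity of those kept is φ(z)/q. The size of the bias is therefore 0.8 × r × φ(z)/q. False-positive rates come from simulation with 4000 trials per setting, facilities of 2, intraclass correlation 0.2 and cluster-robust standard errors.

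| q | φ(z)/q | Bias, r = 0.3 | Bias, r = 0.5 | False positives, r = 0.3 | False positives, r = 0.5 |
|---|---|---|---|---|---|
| 90% | 0.195 | 0.047 SD | 0.078 SD | 6% | 8% |
| 80% | 0.350 | 0.084 SD | 0.140 SD | 8% | 12% |
| 70% | 0.497 | 0.119 SD | 0.199 SD | 10% | 20% |

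In the same settings, intention-to-treat rejects in 5-6% of trials and the complier-average estimate has a bias of about zero.

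**Cross-check by another route.** With no effect, the bias equals p × g, where p = 1 - q and g is the outcome gap in SD between those who would and would not reach 12 sessions. For g = 0.5, p of 10%, 20% and 30% gives 0.05, 0.10 and 0.15 SD, with simulated false positives of 5.9%, 8.4% and 12.0%. The table corresponds to gaps between 0.119/0.30 = 0.40 and 0.078/0.10 = 0.78. A gap of 1.0 is a stronger link than the table assumes and gives larger figures (at p = 20%, 0.20 SD and 16.1%). With g = 0 there is no bias. There is also about none in the adjusted model if attendance depends on the baseline score alone.

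**What the alternative costs.** The complier-average estimate is roughly the intention-to-treat estimate divided by q, and its spread grows likewise: 0.17/0.80 = 0.21 and 0.18/0.75 = 0.24, against 0.17-0.18 undivided; at 70%, 0.18/0.70 = 0.26. If fewer than 12 sessions give half of a true effect of 0.40 SD, it estimates 0.40 + 0.20 × (1 - q)/q: 0.45 at q = 80%, 0.47 at 75% and 0.49 at 70%.

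**The case against.** The per-protocol analysis is supportive. Intention-to-treat is primary, no decision rule rests on the per-protocol result, and showing the two side by side is common practice. Handling of controls and interpretation may be set out in an analysis plan that is not shown. This stands and limits the weight of the point, but the selection rule itself is fixed in the article.

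Size and direction rest on assumptions, and this stands too. A reader might infer that the bias favours music because people who are getting worse stop attending. The documents do not support that: participants could equally stop because they are doing well or are busy. Non-adherence may also be rare, since T2 is postponed until after the final session.

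A reader might also set the bias against the effect size of 0.2 in the Sample Size Calculation. That section names no metric. The stated 67 is nearly reproduced by f = 0.2 in a repeated-measures interaction (66, assuming a correlation of 0.5) and exactly by f² = 0.2 with one predictor (67). A standardised difference of 0.2 between two groups would need 1300 in total. The comparison should not be made.

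Nor does the longer schedule show that the 75% or the content claim is wrong. The natural reading is 12 of the 16 manual sessions, with the others as exploratory extras. An absolute count also suits a minimum-content argument, so redefining adherence as a share of the schedule is not called for.

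Finally, the alternative is not free of bias. By the order in Table 1, someone who stops after session 11 has had all five emotion sessions and five of the six EF sessions, so assuming no effect below 12 is strong. This stands and must be disclosed.

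**Conclusion.** The concern holds as a flaw in a supportive analysis that is cheap to improve. The 12-session rule breaks the randomised comparison by removing people from one arm only. Under the stated assumptions (70-90% adherence, correlation 0.3-0.5, pre-post correlation 0.6), the bias is about 0.05-0.20 SD and the false-positive rate 6-20% when there is no effect. If attendance is unrelated to the later course, there is none. The direction is open. The primary intention-to-treat analysis is untouched, and nothing here suggests that the trial's main conclusion would be wrong.

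**What to change.** - Add a complier-average causal effect at T2 and T3 as the analysis of the effect of receiving the intervention. Use facility allocation as the instrument for reaching 12 sessions, the baseline score as covariate, and facility-clustered standard errors (two-stage least squares or equivalent).
- Keep the per-protocol result if wanted, but label it descriptive and non-randomised.
- State the assumption that fewer than 12 sessions have no effect, and that the estimate overstates the effect if partial attendance helps. Accompany it with a version using the number of sessions attended as the exposure, and state that this assumes an approximately linear dose effect.
- State whether, for participants scheduled for 24-27 sessions, the count of 12 refers to the 16 manual sessions.

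The cost is a few sentences and the two added models per outcome. Attendance is logged after each session, and the article says that analysis will follow its acceptance, so the change can be made before results are seen. The statistical price is the wider interval shown above (spread of the estimate about 0.21-0.24 against 0.17-0.18 SD).

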## Discussion

In this paper, the design of an RCT is presented, which aims at exploring the effectiveness of and experiences with a music intervention for adults with ID and CB on various outcome measures, including CB, well-being, depression, anxiety, self-esteem, and EF. The first strength of this study is that it concerns a clustered RCT design with a sufficient sample size. The second strength is that the multisource data collection, including the use of self-report questionnaires and tests as well as proxy measures, improves the research quality. Third, because distal outcomes (measured over a longer period of time) and proximal outcomes (measured immediately after the intervention) will be used, immediate effects can be assessed too. Lastly, as qualitative data are collected alongside quantitative data, further insight into the process or mechanisms of change can be gained.

However, some limitations also have to be taken into consideration. First, blinding is not possible in the design because the nature of the intervention and the different questionnaires at the data collection points for both groups precludes blinding of the assignment for all parties involved. The absence of an active control condition might entail difficulties in ascribing possibly disclosed effects to power factors of the music intervention, such as level of attention [70]. Furthermore, there are several anticipated challenges, which are based on previous work conducting RCTs with adults with ID. These include challenges with recruiting adequate numbers, resistance to the use of control groups, assessing participants through gatekeepers (ie, the caregivers), and staff turnover that impacts the data collection [25]. The following steps to minimize attrition are considered in this study: (1) the research team follows a flexible participant-led approach to gathering all data—with contacts being at times suggested by participants and at the convenience of the facility of the participant; (2) the incentive to complete all questionnaires and tests is increased with the compliment card that participants receive after every data collection measurement; (3) caregivers will receive multiple reminders, either live, via mail, or telephone, to return the questionnaires on time; and (4) the combination of collecting data from both participants and caregivers reduces the burden for them and diminishes the impact of participant dropout or staff turnover.

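### Facilities are randomised, but the stated mixed model adjusts only for dependence within subjects, so standard errors are too small and p-values too low

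*Protocol article*

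**What the plan says.** Four places in the protocol article bear on this.

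- **Study Design** makes the facility the unit of allocation: "Randomization will be performed at a facility level for 3 reasons". It adds: "There is no maximum number of participants per facility".
- **Sample Size Calculation** treats the resulting correlation as material: "Because cluster randomization negatively affects the power, the sample size needs to be adjusted". It then gives the adjustment: "With the average cluster size of 2 participants per residential facility and allowing an intraclass correlation of 0.2, the adjusted sample size is 80".
- **Discussion** lists as the study's first strength that "it concerns a clustered RCT design with a sufficient sample size".
- **Data Analysis** specifies a linear mixed model restricted to time and the treatment-by-time interaction, with two-sided 5% tests. The stated benefit of the model is "making it possible to adjust for the dependence of the repeated observations within the subjects". Facility is not mentioned in that section.

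**The concern.** In a cluster-randomised trial the treatment contrast is a contrast between facilities. Residents of one facility share an environment and probably staff, and they all receive the same allocation. Part of the difference between arms is therefore chance difference between facilities. A model whose highest level is the participant counts 97 independent units. The number of randomised facilities is nearer 48 (97 divided by the planned average of 2; the achieved number is not reported).

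If that between-facility variation is left out of the model, the standard errors of the T2 and T3 contrasts are too small, the confidence intervals too narrow and the false-positive rate above 5%. This applies to every outcome analysed with this model, in both the intention-to-treat and the per-protocol analysis. The plan also becomes inconsistent: facility correlation counts when participants are recruited but not when the hypotheses are tested.

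**Working it through.** **Inputs from the article.** Average facility size m = 2, ICC = 0.2, unadjusted N = 67, adjusted N = 80, target 96, achieved 97 (44 intervention, 53 control), two-sided α = 0.05.

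**1. The plan's own figures reproduce.** A regression test of one predictor with f² = 0.2, α = 0.05 and power 0.95 needs N = 67. (The article does not say which effect-size metric its 0.2 refers to.) The design effect is DE = 1 + (m − 1) × ICC = 1 + 1 × 0.2 = 1.2. Then 67 × 1.2 = 80.4, stated as 80, and 80 × 1.2 = 96 for dropout. So the plan itself works with a design effect of 1.2.

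**2. Error rate if that design effect is left out of the analysis.**

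- Naive SE / true SE = 1/√1.2 = 0.913, about 9% too small.
- Actual α = 2 × [1 − Φ(1.96/√1.2)] = 2 × [1 − Φ(1.789)] = 0.074.
- Effective sample from 97 participants = 97/1.2 ≈ 81.

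Other ICC values at m = 2 (assumptions): 0.05 gives 5.6%, 0.1 gives 6.2%, 0.3 gives 8.6%. Larger facilities at ICC 0.2: m = 3 gives 9.8%, m = 4 gives 12.1%.

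**3. Allowing for baseline adjustment.** The model has no treatment main effect, so baseline means are constrained equal and the contrast behaves approximately like Y2 − ρY1. Assume total variance 1 and a within-person correlation ρ = 0.5 (not in the article). The variance of Y2 − 0.5·Y1 is then 1 + 0.25 − 2 × 0.5 × 0.5 = 0.75. The facility share depends on how the facility effect behaves over time:

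- constant: 0.2 × (1 − 0.5)² = 0.05
- correlated 0.5 between waves: 0.2 × (1 + 0.25 − 0.5) = 0.15
- independent between waves: 0.2 × (1 + 0.25) = 0.25

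For unequal sizes, DE = 1 + [(1 + CV²)m − 1] × ICC, here with an assumed CV of 0.7, so the multiplier is 1.49 × 2 − 1 = 1.98.

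| Facility effect over time | ICC of the contrast | DE, equal sizes | α, equal | DE, CV 0.7 | α, CV 0.7 |
|---|---|---|---|---|---|
| Constant | 0.05/0.75 = 0.067 | 1.067 | 5.8% | 1.132 | 6.5% |
| Half stable | 0.15/0.75 = 0.20 | 1.20 | 7.4% | 1.396 | 9.7% |
| Varies freely by wave | 0.25/0.75 = 0.333 | 1.333 | 9.0% | 1.66 | 12.8% |

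**4. Simulation of the stated model** (no treatment effect, ICC 0.2, participant-level correlation only, assumed ρ = 0.5). With equal facilities of 2, type I error was 5.2% to 5.8% for a constant facility effect, 7.1% to 7.2% for a half-stable one, and 9.0% to 9.1% for one varying freely by wave. With unequal facility sizes it ranged from 6.3% to 13.4%. At ICC 0 it was 4.9% to 5.6%, with a Monte Carlo standard error of about 0.4 points, so the simulated test itself is close to nominal. These results agree with the table.

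**The case against.** The restriction to time and its interaction with treatment most naturally describes the fixed effects, meaning that the treatment main effect is left out. The word limiting the terms is not attached to the dependence structure, and a fuller plan that is not shown might add a facility random effect. That stands to this extent: a facility effect is not formally excluded. But the article goes on to say which dependence the model handles, and it stops at the participant. An analyst following the text would fit a two-level model. This is a stated analysis that does not match the unit of randomisation, not a detail left for later.

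The second objection concerns size. The 7.4% applies the design effect of a raw outcome to a baseline-adjusted contrast. If facility effects are constant over time, most of the facility variance drops out and the excess is under one percentage point; the lowest simulated value, 5.2%, cannot be told from 5%. That stands too. But constancy cannot be assumed. Challenging behaviour, depression and anxiety are rated by caregivers, and the Discussion expects staff turnover to affect data collection, so a facility's ratings may shift between waves.

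It is also fair that the facility-size distribution and the within-person correlation are assumptions. The extra participants recruited for clustering still add precision, so that effort is not lost.

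**Conclusion.** The concern holds. The stated analysis ignores a level of correlation that the design creates and that the sample size calculation puts at 0.2.

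On the plan's inputs, standard errors are about 9% too small and the false-positive rate is about 7.4%. With equal facilities of 2 the plausible range is from just above 5% to about 9%, depending on how stable facility effects are over time. With uneven facility sizes, which the design allows, it reaches about 13%. The inflation is small if the true ICC is low or facility effects are stable. These ranges rest on an assumed within-person correlation of 0.5 and, for uneven sizes, chiefly on an assumed coefficient of variation of about 0.7. The direction does not depend on those assumptions: positive facility correlation in the contrast pushes towards false positives.

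This should be corrected before the data are analysed. Otherwise the choice between clustered and unclustered p-values is made after both can be seen.

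**What to change.** Amend the Data Analysis section to specify:

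1. A three-level model: observations within participants within facilities, keeping the stated fixed effects.
2. A facility random intercept and a facility-by-wave random effect. The intercept alone is not enough. It captures the constant part of the facility effect, which baseline adjustment already largely removes; the part varying by wave does most of the damage to the T2 and T3 contrasts.
3. Kenward-Roger or Satterthwaite degrees of freedom, given roughly 48 facilities.
4. A pre-stated fallback if the model does not converge, which is a real possibility at about two residents per facility: facility-clustered standard errors with a small-sample correction. In simulation, facility-clustered errors gave about 5% with equal facilities and 5.7% to 6.6% with unequal ones, so they remove most of the excess.
5. The same handling in the per-protocol analysis, and reporting of the number of facilities per arm and the estimated ICC.

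The cost is a few sentences and slightly wider confidence intervals. No new data are needed beyond the facility identifier, and the article states that analysis follows acceptance of the protocol paper.
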